#### Subgroup analysis

Planned subgroup analyses include examining whether the intervention was more efficacious among women in one community versus another. We will also examine if there was a differential impact of the intervention among women who had lower education, lower acculturation level or had lower levels of baseline cervical cancer knowledge. In addition we will also examine if there was a difference among the groups in awareness of their results and among those told of abnormal findings (Pap or HPV), the proportion having had appropriate follow-up testing. We will consider all these to be hypothesis-generating analysis and not definitive since we will lack statistical power for most of these subgroup analyses.

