## Methods

### Participants, interventions, and outcomes

#### Overview and trial design

Our study is a randomized controlled trial of 600 women in three communities in Miami-Dade County (South-Dade, Little Haiti, and Hialeah). Minority women, aged 30 to 65, who have not completed a cervical cancer screening in the past 3 years and who agree to participate in the study have a 30-minute intake visit by one of our two bilingual research assistants (RA). Once they complete our research intake survey, they are randomized into one of three possible interventions. The public health outreach group receives culturally tailored cervical cancer health education materials and brochures indicating locations where low cost Pap smear screening is available (Group 1). The second group undergoes a comprehensive CHW outreach intervention that includes home visits and patient navigation to help women obtain low cost Pap smear screening in their community. The third group receives the comprehensive CHW intervention and the opportunity to have home HPV self-sampling at the time of visit. The primary outcome is self-reported cervical cancer screening (either Pap smear test or via self-sampled HPV screening) determined at a 6-month follow-up assessment done by a RA blinded to study allocation.

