#### Intervention Group 1 – Public health community outreach

As part of our overall efforts aimed at reducing cervical cancer disparities, CHWs in each targeted community have been engaged in public health outreach. These activities include cervical cancer education campaigns over local ethnic radio stations and articles in local ethnic newspapers. The CHWs have also developed health education materials, such as brochures and fact sheets, which they distribute at events such as health fairs, community events, and other such gatherings. These are primarily based on existing materials from the National Cancer Institute (NCI) as well as other sources, such as the American Cancer Society. With feedback and suggestions from our CABs and health educators, these materials are tailored and adopted to the local culture, characteristics, and language of each community. The materials include information about the Pap smear test, why it is important, existing healthcare sources in each community, and how to go about making appointments for a Pap smear. In our study, women randomized to Group 1 are given copies of these brochures at the end of the initial intake visit. They are told the material has information on cervical cancer screening and they are encouraged to read the material. At 3 months these women also receive a brief phone call for continuity and retentions purposes reminding them of the study, obtaining any updated contact information and reminding them that at 6 months they will be called to schedule a follow-up visit by the RA.

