#### Navigation

In addition to health education, a major role for the CHW is to offer women practical assistance that would facilitate her access to screening services. Navigation services may range from explanation of services offered at our participating clinical sites, availability of sliding fees and specific programs for cervical cancer screening for the uninsured (such as the Center for Disease Control early detection breast and cervical cancer screening programs), and assistance with making/scheduling the clinical appointments for the participant. On a case by case level, CHWs may provide assistance with other issues such as transportation (bus routes), potential language, cultural, or even child care issues, and, if requested, accompany the woman to screening appointments. CHWs also make appointment reminder calls the day prior. Within 2 weeks after a woman has the Pap smear screening, CHWs will contact the participant by phone to see if she requires any further assistance. If patients have not been notified of the results, with patient consent, the CHW tries to obtain the information from the FQHC and, with provider approval, may relay findings to the patients (all sites use electronic records). CHWs also play an important role by ensuring that each woman understands her test results. She may also provide further navigation by assisting with additional follow-up as needed, such as for colposcopy (available at each of our sites).

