#### Intervention Group 3: HPV self-sampling option

Women randomized to this arm receive the same health education session as Group 2. In addition, the education includes information on HPV self-sampling as an alternative screening method. They receive an offer of choosing between the HPV screening at the conclusion of the educational session or navigation services to a traditional Pap smear test at a local healthcare facility. If the woman chooses the HPV self-sampling strategy, the CHW provides detailed instructions to complete the sample collection. Using standardized operating procedures and study-specific visual aids and flipcharts we developed, they teach women the proper self-sampling collection technique. Women complete the test in a bathroom while the CHWs wait outside to answer any questions that may arise during the process.

We are using the HPV self-sampling device developed by Preventive Oncology International and the National Institutes of Health, which is a nylon swab 2 cm in diameter and 15 cm in length. Based on prior feedback on comfort and ease of use from earlier study participants, we are using the sampler without the outer sheath. After the woman collects the sample using the swab, she removes the swab out of her vagina and gives it to the CHW. The CHW puts the swab in a pre-labeled liquid media vial (ThinPrep, Holigic Inc., Bedford, MA, US) stirs the sample, caps the bottle, and stores the sample in a re-sealable plastic bag in a locked cabinet. Once a week, the CHW delivers the samples to the University of Miami’s Department of Pathology for processing. The sample is then sent to an outside CLIA approved laboratory (Quest Diagnostics Inc.) for HPV testing. Initially our specimens were being processed by Quest using the Cervista HPV Invader Assay (Holigic In.) [24]. This was later changed to APTIMA HPV Assay (GenProbe Inc.). The former tests for HPV using a DNA based two-step signal amplification method and the latter tests for mRNA using a three step transcription-mediated amplification assay [25]. Both assays test for the 14 HPV strains which have been identified as high risk HPV by the International Agency for Research on Cancer [26] (i.e., 16, 18, 31, 33, 35, 39, 45, 51, 52, 56, 58, 59, 66, 68). They have similar sensitivities for detection of cervical intra-epithelial neoplasia (CIN2+) [27].

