After the specimen is collected, the CHW asks the woman a few additional questions concerning her experience with the procedure, including ease of use, perceived correctness of device use, degree of pain associated with use, and willingness to recommend the device to family or friends as an alternative to Pap smear testing. The CHW also stresses the importance of seeing a health care provider to address any other health issues she identified during their conversations. The CHW also advises the woman that a positive result (i.e., positive for HPV high risk), will require follow-up up to ensure she receives recommended medical care. In rare cases where a submitted sample is deemed as quantity not sufficient by the laboratory, CHW will ask the woman to undergo a second HPV sampling.

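### The exploratory between-arm comparison of follow-up testing is restricted to women told of an abnormal result, a subset formed after randomisation that the interventions themselves reshape

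*Protocol article*

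**What the plan says.** The Subgroup analysis section of the protocol article says that "we will also examine if there was a difference among the groups in awareness of their results" and, in the same sentence, "among those told of abnormal findings (Pap or HPV), the proportion having had appropriate follow-up testing". The natural reading is a comparison of the three randomised arms in both parts. The denominator of the second part is fixed in the text: women told of an abnormal Pap or HPV result. The section closes with a caution: "We will consider all these to be hypothesis-generating analysis and not definitive since we will lack statistical power for most of these subgroup analyses".

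Other sections show how a woman comes to be in that denominator.

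- **Group 1** receives brochures: "The materials include information about the Pap smear test, why it is important, existing healthcare sources in each community".
- **Group 2** receives, in the Overview and trial design section, "patient navigation to help women obtain low cost Pap smear screening in their community".
- **Group 3** has a choice made after randomisation: "They receive an offer of choosing between the HPV screening at the conclusion of the educational session or navigation services". A self-sample positive for high-risk HPV "will require follow-up up to ensure she receives recommended medical care", so it is an abnormal finding for this analysis.
- **Being told** is part of the navigation service: "If patients have not been notified of the results, with patient consent, the CHW tries to obtain the information from the FQHC". The Group 1 section describes no such service.
- **Uptake** is designed to differ. The Sample size section plans for 20 points more in Group 2 than in Group 1, and a further 15 in Group 3 over Group 2. It states no Group 1 rate.

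**The concern.** Randomisation makes the three arms comparable as randomised. It does not make comparable the women who later reach a particular step, when the treatment influences who reaches it. Here each step into the denominator (screened, abnormal, told) lies on the causal path of the intervention. A difference between arms in the proportion followed up could therefore reflect better or worse follow-up, a different kind of woman being drawn into screening, or a different kind of abnormality being found. The planned proportion cannot separate these.

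Whether self-sampling leads on to completed care is the obvious next question after an uptake result. The protocol raises a related worry under Secondary outcomes, where it asks whether a negative self-sample could weaken contact with providers. Readers are thus likely to give this exploratory figure more weight than its label suggests.

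**Working it through.** The documents state no figure for this analysis, so there is none to reproduce. The check has three steps.

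**1. Is the subset affected by the intervention?** The expected number told in an arm is N × P(screened) × P(abnormal | screened) × P(told | abnormal). From the protocol, P(screened) is designed to differ between arms. P(abnormal) depends on the test, and the mix of tests differs in Group 3. P(told) is acted on by a service that Group 1 is not described as receiving. All three factors can differ by arm.

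**2. Can selection alone move the planned proportion?** From the documents: increments of +20 and +15 points and 600 women in total. Assumed: 200 per arm (the allocation ratio is not stated); Group 1 uptake of 30%, giving 30/50/65%; half the women engaged with care and half hesitant; 10% abnormal whatever the test; all told. Uptake (engaged/hesitant) is 60%/0%, 80%/20% and 80%/50%. Follow-up (engaged/hesitant) is 80%/30% in Group 1 and 85%/35% in both Groups 2 and 3.

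| | Group 1 | Group 2 | Group 3 |
|---|---|---|---|
| Screened | 60 | 100 | 130 |
| Told (engaged + hesitant) | 6 + 0 | 8 + 2 | 8 + 5 |
| Followed up | 6 × 0.80 = 4.8 | 8 × 0.85 + 2 × 0.35 = 7.5 | 8 × 0.85 + 5 × 0.35 = 8.55 |
| Followed up / told | 80% | 75% | 66% |
| Completed pathway, (screened − told + followed up)/200 | 58.8/200 = 29.4% | 97.5/200 = 48.8% | 125.55/200 = 62.8% |

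Within each type of woman, follow-up in Groups 2 and 3 is identical, and 5 points better than in Group 1. Yet the conditional proportion falls from arm to arm.

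The gap between Groups 2 and 3 equals the engaged-minus-hesitant difference in follow-up times the change in the hesitant share: 0.50 × (5/13 − 2/10) = 0.50 × 0.185 = 9.2 points. With a difference of 0.25 it is 4.6 points, and with no difference it is zero. If the additional women were more inclined to attend follow-up, the sign would change. A common abnormality rate cancels out of this gap.

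**3. Which all-randomised measure should replace it?** Assume 200 per arm and Group 1 uptake of 20%, so 40% and 55% in Groups 2 and 3; 5% of Pap and 15% of HPV tests abnormal; in Group 3, 90 women choosing HPV and 20 choosing Pap; 3 women followed up in Group 2 and 9 in Group 3.

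- Group 2: 80 screened, 80 × 0.05 = 4 abnormal, 3/4 = 75% followed up.
- Group 3: 110 screened, 90 × 0.15 + 20 × 0.05 = 14.5 abnormal, 9/14.5 = 62% followed up.
- *Abnormality found and followed up*, per woman randomised: 3/200 = 1.5% v 9/200 = 4.5%. Group 3 stays ahead until its follow-up falls below 3/14.5 = 21%. Even at 30% follow-up it scores 14.5 × 0.30/200 = 2.2% against 1.5%. The measure rewards the test that returns more positives.
- *Completed pathway*, per woman randomised: (80 − 4 + 3)/200 = 39.5% v (110 − 14.5 + 9)/200 = 52.3%, against 40% v 55% simply screened. At 30% follow-up Group 3 drops to (110 − 14.5 + 4.35)/200 = 49.9%. Missed follow-up counts against the arm, as it should.

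**The case against.** The strongest reply is that the conditional proportion answers a fair question: of women told of a problem, how many went on to follow-up testing? In step 3 the Group 3 women are assumed to be followed up less often, and the planned figure reports just that. Its disagreement with a per-randomised figure shows two different questions, not an error. This stands. A reader might infer that the planned comparison will point the wrong way, but the documents do not support that. Step 2 shows that selection alone can shift the figure, and it does so only with strata that are wholly assumed.

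A reader might also infer that each arm uses a different test. That is too strong. Groups 1 and 2 are both directed to Pap, and only Group 3 has a different mix. No document figure says how many Group 3 women will choose self-sampling. The Background notes a 2012 recommendation for HPV testing alongside cytology, so HPV results could arise in the other groups too.

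Nor does the same criticism reach awareness of results. No denominator is stated for it, and an article may leave that to the fuller plan.

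The analysis is labelled hypothesis-generating and is neither the primary nor a secondary outcome. With counts as small as 4 women told in an arm, where one woman moves the result by 25 points, the caution about power is apt. But it is a caution about precision. More women would narrow the interval around the same selected contrast.

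Finally, the completed pathway lies close to the primary outcome and so adds limited information by itself. That is a reason to show the cascade and the conditional figure beside it, not to test the conditional figure between arms.

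**Conclusion.** The point holds in limited form. The protocol fixes an exploratory between-arm contrast on a denominator that forms after randomisation and whose size and make-up the intervention changes, and its stated caveat does not cover this. The structural conclusion rests on the protocol's own text and needs no assumed rate.

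The size and direction of any distortion cannot be derived from the documents. The 0 to 9 point range for Group 2 against Group 3 depends on the assumed strata, uptake split and follow-up rates. The 40% and 55% uptake levels in the working are likewise not planned rates, since the Sample size section gives only differences.

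The consequence is confined to how one exploratory result is read. It is a worthwhile improvement and does not threaten the trial's main conclusions.

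**What to change.** In the Subgroup analysis section, or in the analysis plan that implements it:

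1. Make the between-arm comparison on all randomised women, using the completed screening pathway: screened and, if abnormal, followed up.
2. Show for each arm the numbers randomised, screened, abnormal, told and followed up.
3. Keep the proportion followed up among women told of an abnormality, split by Pap or HPV, as a descriptive figure without a between-arm test.
4. Do not use abnormality found and followed up, per woman randomised, as the sole comparison.
5. Add to the hypothesis-generating caveat that the conditional figure is subject to selection after randomisation, as well as low power.

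The cost is wording and one extra table, with no change to visits or interventions. One small rule is needed: how a woman who was screened but does not know her result is counted. Showing that number separately in the cascade would make the choice visible. What counts as appropriate follow-up is a clinical definition and is left as the protocol has it.

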#### Cost analyses

Although the study does not include a formal cost effectiveness analysis, we will provide estimates of the cost of screening an individual woman in the each of the intervention arms. To calculate a total cost for each group we will assess the resources that were used in the project. This will include all personnel time, including personnel time devoted to training the RAs and CHWs, RA and CHW time (e.g., time spent assessing eligibility, managing contacts, recruiting, conducting the intervention, and administrative time), and resources used such as space, supplies, and medical care. For each of the different types of resource utilization, including personnel time, we will establish a standardized price for a unit of that resource. The cost of the medical care categories will be obtained by either i) the actual cost (e.g., for analyzing the self-samplers) or ii) the average cost of Pap smears at the clinics where testing was done. Total costs for each activity or supply will be calculated by multiplying the units used by the standardized “price”. Costs that are not attributable to a single arm, such as personnel time for training the CHW and RA, will be divided equally among the three arms of the project, or allocated as best estimated by resource use intensity of each arm. Total costs for each of these arms will be calculated using the information on resource utilization and standardized prices. Then an average cost per participant, and per woman screened, for each group can be obtained. From knowing the cost per woman screened in each arm, we can determine the additional cost of screening additional woman in Groups 2 and 3 as compared to the group simply receiving public health outreach.

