#### Allocation and blinding

Once women complete the intake questionnaire they are randomized into one of three possible interventions by the study coordinator who has the pre-generated randomization list from the study statistician. As the study design is hierarchical, with each participant nested within a site, the randomization is based at the site level. A study coordinator notifies the CHW assigned to that woman of the group assignment, and the CHW then follows-up with the women within a week, informing them of their assignment. If women are randomized to Groups 2 or 3, a follow-up visit is scheduled, ideally no later than a month from randomization. The RA who conducts the initial intake visit and 6-month follow-up assessment is blinded to study allocation. However, both women and CHWs are aware of the group to which each participant was randomized.

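### Cost per woman screened includes the research assistants' training and time, which is nearly all trial cost; this inflates the lowest-uptake arm most and could change how the arms rank

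*Protocol article*

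**What the plan says.** All costing rules are in the Cost analyses section of the protocol article.

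- **Target.** The section disclaims a formal cost-effectiveness analysis, but states that "we will provide estimates of the cost of screening an individual woman in the each of the intervention arms".
- **What is counted.** Resources include "all personnel time, including personnel time devoted to training the RAs and CHWs, RA and CHW time", and the examples given are "time spent assessing eligibility, managing contacts, recruiting, conducting the intervention, and administrative time". Space, supplies and medical care are added.
- **Shared costs.** Costs not attributable to one arm, "such as personnel time for training the CHW and RA", are to be "divided equally among the three arms of the project, or allocated as best estimated by resource use intensity of each arm". No rule is given for choosing between the two options.
- **Outputs.** Each arm's total is divided by participants and by women screened. The extra cost of screening additional women in Groups 2 and 3 compared with Group 1 is then to be worked out from the per-screened figures.

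The RA's role is described elsewhere. Under Allocation and blinding: "The RA who conducts the initial intake visit and 6-month follow-up assessment is blinded to study allocation". The sections on the intake visit, the 6-month evaluation and consent add verification of eligibility, consent and two structured interviews. The education session, navigation and self-sampling are delivered by community health workers (CHWs), as the sections on Groups 2 and 3 state.

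**The concern.** The named target is a cost of screening, and the counting rule takes in the cost of measuring whether screening happened. An outreach programme would not pay for research consent, an intake survey or a blinded outcome interview. This is an explicit inclusion, not a detail that a condensed article leaves out.

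The inclusion is not neutral between arms. RA work is by design about the same for every randomised woman, but the divisor is the number of women screened, and the trial is planned around large differences in that number. The arm with the fewest women screened carries the largest research charge per woman screened. If Group 1 has the lowest uptake, brochure outreach may look as costly as navigation or self-sampling, or costlier, when its delivery is the cheapest. The additional cost of Groups 2 and 3 would be distorted as well if it is obtained by subtracting the per-screened averages.

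**Working it through.** The article states no cost figure, so there is nothing of its own to reproduce. The check asks how a common research cost passes through the planned division.

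**Inputs from the article.** Uptake differences are 20 points (Group 2 over Group 1) and a further 15 points (Group 3 over Group 2), from Sample size. There are 600 women, three CHWs with two weeks of training each, two RAs and 40 months of recruitment.

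**Assumptions.** Group 1 uptake p1 is 0.10 to 0.40, so p2 = p1 + 0.20 and p3 = p1 + 0.35. Delivery cost v per woman (Groups 1/2/3) is $5/60/80, $5/100/120 or $10/150/150. There are 200 women per arm. RA cost R is equal per woman. Laboratory cost per screened woman is left out, which does not affect the comparison only if it is similar across arms.

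**Formula.** Cost per woman screened = (v + R)/p, so research cost adds R/p.

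**Worked case**, p = 0.20/0.40/0.55 and v = $5/100/120:

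| R | Group 1 | Group 2 | Group 3 | Cheapest first |
|---|---|---|---|---|
| $0 | 5/0.20 = $25 | 100/0.40 = $250 | 120/0.55 = $218 | 1, 3, 2 |
| $50 | 55/0.20 = $275 | 150/0.40 = $375 | 170/0.55 = $309 | 1, 3, 2 |
| $100 | 105/0.20 = $525 | 200/0.40 = $500 | 220/0.55 = $400 | 3, 2, 1 |

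**Where the order changes.** Groups i and j swap at R* = (v_j p_i − v_i p_j)/(p_j − p_i). In the worked case, Group 1 against Group 2 gives (100 × 0.20 − 5 × 0.40)/0.20 = $90, and Group 1 against Group 3 gives (120 × 0.20 − 5 × 0.55)/0.35 = $61. Over p1 = 0.10 to 0.40:

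| v (Groups 1/2/3) | Group 1 dearer than Group 2 above | Group 1 dearer than Group 3 above |
|---|---|---|
| $5/60/80 | $23 to $105 | $16 to $81 |
| $5/100/120 | $43 to $185 | $28 to $126 |
| $10/150/150 | $60 to $270 | $30 to $150 |

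Below these values Group 1 keeps its place.

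**Is R of this size plausible?** Two RAs full time for 40 months at an assumed 160 h a month and $20/h cost 2 × 40 × 160 × $20 = $256,000, or about $427 per woman over 600 women. R = $100 is $60,000, about 23% of that effort. Actual RA effort is not stated, so this shows plausibility only.

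**Additional cost (worked case).** Subtracting per-screened averages gives 250 − 25 = +$225 (Group 2 vs 1) and 218 − 25 = +$193 (Group 3 vs 1) at R = 0. At R = $100 it gives 500 − 525 = −$25 and 400 − 525 = −$125. The ratio of differences is (100 − 5)/0.20 = $475 and (120 − 5)/0.35 = $329 at any R, because R cancels.

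**CHW training split.** At an assumed 40-hour week and $20/h, training costs 3 × 80 × $20 = $4,800. Split equally, that is 4,800/600 = $8 per woman. At the opposite extreme, with nothing to Group 1, it is 4,800/400 = $12 in Groups 2 and 3. With R = 0 in the worked case:

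- Equal split: $65/270/233 per woman screened, with incremental ratios of $475 and $329.
- Nothing to Group 1: $25/280/240, with ratios of $535 and $363.

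The ranking is the same under both. It also holds at $50/h: $125/300/255 against $25/325/273. The extreme is a bound and not a recommendation, since Group 1 also uses CHW work.

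**The case against.** The analysis is descriptive, sits outside the primary and secondary outcomes, and can be read as an all-in costing of the project. Costs are to be built up by activity, so research and delivery could still be separated at reporting. An equal R does not touch a properly formed incremental ratio. All of that stands, and it limits the point's importance. It does not make a figure that contains outcome interviews a cost of screening.

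Four stronger readings are tempting, and the article does not support them.

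- **That the ranking will reverse.** This depends on prices, RA cost and Group 1 uptake, none of which is given. At R = $50 in the worked case Group 1 is still cheapest.
- **That the equal split of training is the default.** The same sentence offers allocation by resource-use intensity and prefers neither. The training split alone did not change ranks in the cases tried.
- **That Group 1 should carry no CHW training cost.** The section on the CHWs has them assisting in all three arms, the training covers outreach and cancer education, and the Group 1 section credits them with developing the materials.
- **That the figure would mostly measure research overhead.** In the worked case at R = $100 the research share is 100/105 = 95% in Group 1, but 100/200 = 50% in Group 2 and 100/220 = 45% in Group 3. The true R is unknown.

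Nor is it certain that RAs deliver nothing. Group 1 brochures are handed over at the end of the intake visit, which the RA conducts. The article does not say who hands them over. Removing all RA time could therefore take out a few minutes of genuine Group 1 delivery.

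**Conclusion.** The point holds in a limited form. The counting rule does not match the stated target, because RA training and RA time are almost entirely research cost. A charge of about R per randomised woman adds R/p per woman screened. At an assumed p1 of 0.20 that is 5.0R, 2.5R and 1.8R in Groups 1, 2 and 3, so Group 1 is inflated most. The order of arms could change at R between about $16 and $270, depending on assumed delivery costs and Group 1 uptake; below the relevant threshold it does not. An additional cost formed by subtracting per-screened averages is also distorted, while a ratio of differences is not. The result rests on RA effort being about equal across arms. Leaving the training allocation open is a lesser matter: it shifts values, not ranks, in the cases tried. The trial's main conclusions are unaffected, but the correction is cheap and arm-level cost bears on which outreach approach a community would choose.

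**What to change.** In Cost analyses:

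1. Report delivery cost per arm without RA training, RA time and other trial-only activity such as consent and research interviews. Keep any intake-visit minutes spent handing out Group 1 brochures.
2. Show research cost on a separate line, and the all-inclusive figure as a sensitivity result.
3. For shared CHW training, make the plan's second option, allocation by resource-use intensity, the main rule, with Group 1 bearing its share. Show the equal split as a sensitivity analysis.
4. State that additional cost versus Group 1 is the difference in total cost divided by the difference in women screened, with arms put on a common number of participants.

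The cost is a change of wording and a re-tabulation of resources already to be costed by activity, with no new contact with participants. The downside is some judgement in separating research from programme time, chiefly for CHW eligibility and recruitment work; the rule used should be stated.
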